### (VI) Neuropsychological tasks

#### Flanker task

In the **Flanker task** (Figure 4, upper panel), stimuli consist of five arrows. The middle arrow is the target stimulus and participants should indicate via button press with the right or with the left hand if the target arrow points to the right or to the left. The outer arrows serve as distractors and can point in the same direction (*congruent trial*) or in the opposite direction (*incongruent trial*). Each block consists of 184 trials and has a duration of 4.5 minutes, with 50% of the trials being congruent and incongruent. Stimuli are presented for 60 ms and participants have 1360 ms to respond. The interstimulus interval is 1460 ms. During the intervention (V1-V10) the task will be presented for four blocks. However, during baseline (V0), post-stimulation (V11) and follow up (V12) sessions, the task will be presented for two blocks (about 10 minutes) to minimize strain for the participants, since the CPT and the n-back task will be also presented during these visits to test for transfer effects.

#### N-back task

We will use the **n-back task** (Figure 4, right lower panel) with  $n=2$ . For this purpose, a series of objects will be presented with 25% of the trials being target trials meaning that the current stimulus is identical with the stimulus two trials earlier. Thus, the task requires continuous processes of encoding, retrieving and updating contents of working memory. The presented objects in each block consist of 10 different photographs that are presented 10 times each and serve as a target twice. Each trial has a duration of 2400 ms of which each object is displayed for 500 ms, preceded by a fixation cross for 1900 ms. The task will be conducted for 3 runs (5 minutes per run) with 1 min. pauses in between.

[figure not shown]

Figure 4. Examples of single trials of the Flanker task, the Continuous Performance task (V0, V11, V12) and the n-back working memory task

#### Continuous performance task

In the **Continuous performance task** (CPT) (Figure 4, left lower panel), various upper case letters will be presented. One of the letters will be defined as a cue and one as a target stimulus. Whenever the cue is followed by the target stimulus, participants are instructed to press a button. However, participants should withhold their response if the cue is followed by another stimulus. The task will consist of 3 runs á 4.5 minutes (80 stimulus sequences per run, 20 target sequences, 20 non-target sequences) with short breaks in between. For each trial the stimulus is presented for 150 ms and participants have 1400 ms to give their response (interstimulus interval = 1650 ms).

Task performance during each intervention will be assessed (accuracy, commission and omission errors, reaction time and reaction time variability, **Study A:** n-back task, **Study B:** Flanker task) to control for potential learning and motivational effects.

## 7.4 End of study and termination

### 7.4.1 Regular end of study

The study ends with the last follow-up visit of the last patient.

### 7.4.2 Premature end of study

#### 7.4.2.1 Withdrawal of study subject

##### Decision of study subject

Children and adolescents as well as their caregivers can refrain at any time and without providing reasons from study participation. They will be informed that their concurrent or subsequent treatment

will not be affected or compromised because of the patient's decision. All participants will be offered a final physical examination once they participated in at least one intervention session and regardless after which visit they decided to stop participation.

All randomised patients will be asked to provide their consent to be assessed for the primary outcome, in particular, those who discontinue treatment prematurely to keep missing data due to loss to follow-up at a minimum.

#### ***Decision of investigator or Sponsor***

Moreover, the investigator can decide to end study participation if there is reason to assume that the intervention is harmful for the child/adolescent or that study participation is mainly motivated by the parent and is not wished for by the child/adolescent. Reasons for exclusion from the study will be documented in the electronic Case Report Form (eCRF).

#### ***Compliance***

Patients who are non-compliant to a degree that either their safety or the integrity of data is at risk, may be excluded from further treatment at the investigator's discretion. This includes intake of medication during the study, aiming to destroy stimulation equipment, and voluntary random responses to the tasks. If possible, assessment of primary outcome will be done.

#### ***7.4.2.2 Termination of study at a study site***

Both the investigator and the Sponsor reserve the right to terminate the trial at any time. Should this become necessary the procedures will be agreed upon after consultation between the two parties. In terminating the trial, the Sponsor and the investigator will ensure that adequate consideration is given to the protection of the best interests of the patients. Regulatory authority and EC will be informed.

The clinical trial can be terminated prematurely at the trial site by the responsible investigator, if

- the continuation of the clinical trial is considered as ethically and/or medically not acceptable
- the resources to continue the clinical trial are not sufficient anymore

### ***7.5 Continued treatment and medical care of subject after end of study***

Patients who are in care at the investigating sites will be able to continue their previous treatment after the end of the study. Participants who were referred to our study from other sources will receive counselling or intervention, as needed.

## **8 EFFICACY AND SAFETY**

### ***8.1 Assessment of efficacy***

In both studies, accuracy in a neuropsychological task is employed to assess treatment efficacy. In **Study A** an n-back task is used to investigate working memory performance, in **Study B** accuracy in a Flanker task provides information on cognitive interference control. Presentation of task-relevant stimuli is realized in Presentation© (version 19, Neurobehavioral Systems Inc., [www.neurobs.com](http://www.neurobs.com)). Presentation© offers the opportunity to receive a detailed logfile of the nature and occurrence of all events during the experiment (stimuli, responses, correction of responses). Using e.g. MatlabR2009b (TheMathWorks, Natick, MA), overall accuracy for congruent and incongruent trials will be determined. Participants will obtain time to practice the task. From the practice trials the investigator can judge whether the participant has understood and is able to perform the task. The tasks will be also employed during the intervention session. To avoid fatigue and boredom, the employed stimuli per task will change across the course of the ten sessions. The n-back task for example will use set of different pictures, in the Flanker task arrows and arrow background will change in color. Stimuli during baseline (T2), post (T3) and follow-up (T4) assessment, however, will be identical.

### ***8.2 Assessment of safety***

Safety and tolerability of tDCS are assessed by (1) a standardized safety questionnaire (Poreisz et al., 2007) as well as (2) EEG recordings before and after tDCS. Moreover, participants are asked at each visit (following the screening) whether they have experienced AE.

## **8.3 Adverse events**

### **8.3.1 Adverse event**

Adverse events (AE) are defined as any untoward medical occurrence in a clinical investigation subject after contact with the investigational medical device (IMD) which does not necessarily have a causal relationship with this treatment. This includes unfavourable signs and/or symptoms, exacerbation of the investigated condition and newly diagnosed conditions during trial participation.

#### **8.3.1.1 Documentation and evaluation**

The investigator must record all AE in the Adverse Event Log provided in the eCRF with information about the following aspects (as described):

##### **Adverse event**

AE should be recorded as diagnoses, if available. If not, separate signs and symptoms should be recorded. One diagnosis/symptom should be entered per record. If a patient suffers from the same adverse event more than once and the patient recovers in between the events, the AE should be recorded separately. If an adverse event changes in intensity, a worst-case approach should be used when recording the event, i.e. the highest intensity and the longest duration of the event.

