**Baseline visit (Visit 0, within 4 weeks after screening)**

- Assessment of arousal, mood and motivation before and after the session (SAM, VAS, diary)
- Resting state, 64-channel EEG
- Neuropsychological performance (tasks: n-back, Flanker, CPT), 64-channel EEG
- Assessment of adverse events
- Randomization

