##### **Date and time of onset**

The date of onset is the date when the first sign(s) or symptom(s) were first noted. If the adverse event is an abnormal clinically significant laboratory test or outcome of an examination, the onset date is the date the sample was taken or the examination was performed. For pre-existing clinically significant conditions (diagnosed or observed as a result of the screening procedures) becoming worse after IMD application the date of onset is the date the worsening began.

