#### 7.5. Safety analyses

For safety evaluations, we will use descriptive statistics for each study (**Study A** and **Study B**) separately and combined. We will tabulate absolute and relative frequencies of adverse events (AEs) and severe adverse events (SAEs) by study arm (tDCS and sham), severity and investigator-assessed relation to investigational treatment. No statistical tests will be performed for (S)AEs which are expected to be rare. In addition, safety and tolerability of tDCS stimulation will be evaluated with the standardized safety questionnaire and differences between study arms (tDCS and sham) will be analyzed in an analogous way to endpoint analysis. We will visualize empirical findings with bar charts and box plots.

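### An unresolved event logged before the first stimulation that worsens afterwards keeps its pre-device onset date and a single intensity and causality rating, because re-dating is limited to clinically significant screening findings

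*Combined protocol and SAP*

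**What the plan says.** Four parts of the plan bear on this.

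- **Definition.** Protocol 8.3.1 defines an AE as "any untoward medical occurrence in a clinical investigation subject after contact with the investigational medical device (IMD"), so the definition starts at device contact.
- **Collection.** Under protocol 8.2, "participants are asked at each visit (following the screening) whether they have experienced AE". Section 7.2 lists "Assessment of adverse events" at the baseline visit, and the examination plan (section IV) marks AE documentation at V0 and V0_MRI. Both come before the first stimulation at V1.
- **Recording.** Protocol 8.3.1.1, under Adverse event: "If an adverse event changes in intensity, a worst-case approach should be used when recording the event", meaning the greatest intensity and the longest duration. A second record is opened only if the patient has recovered before the same event returns.
- **Onset.** Protocol 8.3.1.1, under Date and time of onset: "The date of onset is the date when the first sign(s) or symptom(s) were first noted". The one exception that dates a worsening from when it began is "For pre-existing clinically significant conditions (diagnosed or observed as a result of the screening procedures) becoming worse after IMD application".

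SAP 6.2 makes the number, type and severity of AEs part of the primary safety endpoint. SAP 7.5 tabulates AEs by arm, "severity and investigator-assessed relation to investigational treatment". The SAP sets no filter on onset date and defines no treatment-emergent AE.

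**The concern.** Safety and tolerability under stimulation are a primary objective. A symptom that was mild before V1 and worsens during the sessions is part of what the AE log should show. The exception for worsening covers only clinically significant conditions found at screening, while AE documentation begins at V0. An event that appears in between falls outside the exception and is handled by the first-sign and worst-case rules.

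The resulting record joins a pre-device period and a stimulation period. It has one onset date, one intensity and one causality rating, and from the log alone nobody can later tell when the worsening began. The causality field then asks about an event that started before the device was used, although the clinically relevant change may have come afterwards. The window also includes time off stimulants: section 5.2.3 asks for abstinence from at least two weeks before V0.

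**Working it through.** No sample size, power or event figure in the plan bears on this. The check compares the rules and adds up the visit windows.

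**1. Length of the window** (examination plan, section IV). Screening to V0 is up to 4 weeks and V0 to V1 is up to 4 weeks. 4 + 4 = up to 8 weeks between screening and first device contact.

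**2. What the recording and onset rules give for each course of an event**

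| Course | Records | Onset date |
|---|---|---|
| Clinically significant condition found at screening, worsens after device use | Covered by the exception | Date worsening began |
| Starts after the first stimulation | One | After device contact |
| Starts before V1, resolves, recurs after V1 | Two | Second record after device contact |
| Starts between screening and V1, logged before V1, unresolved, worsens after V1 | One, at highest intensity | Before device contact |
| Screening finding not clinically significant, logged as an AE before V1, worsens after V1 | One, at highest intensity | Before device contact |
| Starts before V1, worst before V1, milder afterwards | One, at pre-device intensity | Before device contact |

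The first three rows are handled properly. Rows four and five lose the date of worsening and a separate rating of it. Row six carries an intensity reached before the device was used into the by-arm severity table.

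**3. Does the definition in 8.3.1 already prevent this?** Read alone, it would: an event at V0 would not be an AE, the worst-case rule would not reach it, and the later worsening would be the first AE. But the plan schedules AE documentation at V0 and V0_MRI. And if the definition alone re-dated every worsening after device contact, the exception in the onset rule would not be needed. Since that exception re-dates one class only, other worsening falls under the first-sign rule. The two readings conflict, and five sites could record the same course differently.

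**4. A further inconsistency.** The outcome categories in 8.3.1.1 count a return to the state at treatment start as recovered. The outcome field therefore uses treatment start as its reference, while the onset field does not.

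**5. Size.** The documents give no share of children with an event ongoing at V1. Assuming 5%, 10% or 20%, each arm of 50 would have 50 × 0.05 = 2.5, 50 × 0.10 = 5 or 50 × 0.20 = 10 such children; for both arms of one study, 5, 10 or 20 of 100. These count children with an ongoing event. Those whose event then worsens are a subset of unknown size.

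**The case against.** The strongest counter-argument is the definition in 8.3.1: a pre-device event is not an AE, so nothing is merged. Step 3 shows why this does not settle the matter, though it does place the root of the problem in the mismatch between the definition and the collection schedule. The worst-case rule is not at fault by itself.

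Other objections stand and limit the point:

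- **The affected set is narrow.** Significant screening findings are re-dated, later events have a post-device onset anyway, and an event that resolves and recurs gets its own record. Since ADHD is diagnosed at screening, its worsening is arguably covered.
- **The event is not lost from the tables.** A reader might infer that merged records would be dropped as pre-device or rated unrelated. The documents do not say so. SAP 7.5 has no onset filter, and the safety set in SAP 5.1 is defined by patient. Causality rests on any evidence or argument for a link, and under 8.4.1 an event counts as an adverse effect if a link is possible or cannot be excluded. An investigator may rate the merged record as related.
- **It is not specific to active tDCS.** The same rules apply to sham under blinding, so the documents do not support inferring a bias in favour of the device.
- **Another source carries timing.** The safety questionnaire is completed at every session from V1 to V10 and compared between arms. For the sensations it covers, worsening can be placed by session. It addresses discomfort during stimulation, however, so it does not replace the AE log for events between sessions.

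**Conclusion.** The point holds in a limited form and is worth fixing. For an unresolved event logged before V1 and outside the screening exception, the rules as written give one record with a pre-device onset, the highest intensity and one causality rating. The event remains in the planned counts. What the AE log loses is the date of worsening and a separate intensity and causality rating for it; intensity and relation are both tabulated in SAP 7.5 for a primary safety endpoint. In the other direction, an event at its worst before V1 is tabulated at its pre-device intensity.

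This rests on taking the collection schedule, rather than the definition in 8.3.1, as governing what sites log at V0 and V0_MRI. The frequency is unknown and both arms are affected. The range of about 3 to 10 children per arm of 50 is an assumed ceiling: it counts ongoing events, and it would be wrong to read it as the number of missed device effects.

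**What to change.** Three changes to protocol 8.3.1 and 8.3.1.1, repeated in the eCRF completion guidance:

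1. Reconcile the AE definition with documentation from V0 by stating how events before the first stimulation are classified.
2. Extend the re-dating rule to any condition or event present before first device application, whichever visit found it and whether or not it was clinically significant. If it worsens after the first stimulation at V1, open a new AE record with onset at the date of worsening and its own intensity and causality.
3. Apply the worst-case rule only within the pre-device period or within the post-device period, never across the two.

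The cost is one or two sentences of protocol text and eCRF guidance, and a few additional AE records. Design, sample size and efficacy analysis do not change. The change has to be made at recording, because a later onset cut in the analysis cannot recover the date of worsening from a merged record.

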##### **Date and time of onset**

The date of onset is the date when the first sign(s) or symptom(s) were first noted. If the adverse event is an abnormal clinically significant laboratory test or outcome of an examination, the onset date is the date the sample was taken or the examination was performed. For pre-existing clinically significant conditions (diagnosed or observed as a result of the screening procedures) becoming worse after IMD application the date of onset is the date the worsening began.

##### **Intensity**

The intensity of an adverse event must be classified using the following 3-point scale:

- Mild: Awareness of signs or symptoms, but no disruption of usual activity.
- Moderate: Event sufficient to affect usual activity (disturbing).
- Serious: Inability to work or perform usual activities (unacceptable).

##### **Causal Relationship to IMP**

The possibility of whether the IMD application caused the adverse event must be classified as one of the following:

##### Reasonable possibility:

There is evidence or argument to suggest a causal relationship between the IMD application and the adverse event. The adverse event may occur as part of a physiological or psychological effect of the IMD or may be unpredictable in its occurrence.

##### No reasonable possibility:

There is no reasonable evidence or argument to suggest a causal relationship between the IMD application and the adverse event.

##### **Action Taken to IMD**

The action taken to the IMD application in response to an adverse event must be classified as one of the following:

- No change (application schedule maintained or no action taken)
- Withdrawn
- Interrupted

##### **Other Action Taken**

AE requiring therapy must be treated with recognised standards of medical care to protect the health and well-being of the patient. Appropriate resuscitation equipment and medicines must be available to ensure the best possible treatment of an emergency situation. If medication is administered to treat the adverse event, this medication should be entered in the Concomitant Medication Log.

##### **Date of Outcome**

The date the patient recovered or died.

##### **Outcome**

The outcome of an adverse event must be classified as one of the following:

- Recovered (fully recovered or the condition has returned to the level observed at initiation of trial treatment)
- Recovered with sequelae
- Recovering
- Not recovered
- Fatal

#### **8.3.1.2 Reporting pathways, responsibilities and deadlines**

According to national law it is the Sponsor's responsibility to provide AE-listings to Competent Authorities.

### **8.3.2 Serious adverse events**

Any untoward medical occurrence in a clinical investigation experienced by the subject, the person applying the medical device or a third party after contact with the IMD, which does not necessarily have a causal relationship with this treatment, which directly or indirectly could have led or could lead to:

- death,
- a life-threatening situation,
- inpatient hospitalisation or prolongation of existing hospitalisation,
- persistent or significant disability/incapacity or a congenital anomaly/birth defect.

#### **8.3.2.1 Documentation and evaluation**

When documenting SAEs the following points are mandatory: SAEs must be documented in the Adverse Event Log in the eCRF as well as on the SAE form. All AEs /SAEs have to be evaluated by the investigator.

#### **8.3.2.2 Reporting pathways, responsibilities and deadlines**

##### **Reporting of serious adverse events (SAE) by the Investigator**

All SAEs must be reported **immediately** to the Sponsor as soon as they become known to the investigator and not later than within 24 hours of their knowledge of the occurrence of the SAE. The SAE Report Form is included in the ISF, and must be completed and submitted according to the instructions provided on the form. The investigator is responsible for submitting the completed SAE Report. In case initial reports are incomplete, a follow-up report must be sent to the Sponsor within 8 calendar days.

Additional information relevant to the SAE such as hospital records, results from investigations, e.g. laboratory parameter, invasive procedures, scans and x-rays, and autopsy results can be faxed or scanned and e-mailed to the Sponsor. In any case this information must be supplied by the investigator upon request from the Sponsor. On any copies provided, details such as patient's name, address, and hospital ID number should be concealed and instead patient identification numbers should be provided.

##### **Reporting of serious adverse events by the Sponsor**

All SAE-Reporting will be performed by the Sponsor according to the national law(s). The detailed processes of SAE-reporting and responsibilities are recorded in a separate SAE-Manual. **SAEs with a causal relationship** have to be reported **immediately** by the Sponsor to the Competent Authority.

